## Abstract

**Introduction:**

Degenerative cervical myelopathy (DCM) is a common and disabling condition of symptomatic cervical spinal cord compression secondary to degenerative changes in spinal structures leading to a mechanical stress injury of the spinal cord. RECEDE-Myelopathy aims to test the disease-modulating activity of the phosphodiesterase 3/phosphodiesterase 4 inhibitor Ibudilast as an adjuvant to surgical decompression in DCM.

**Methods and analysis:**

RECEDE-Myelopathy is a multicentre, double-blind, randomised, placebo-controlled trial. Participants will be randomised to receive either 60–100 mg Ibudilast or placebo starting within 10 weeks prior to surgery and continuing for 24 weeks after surgery for a maximum of 34 weeks. Adults with DCM, who have a modified Japanese Orthopaedic Association (mJOA) score 8–14 inclusive and are scheduled for their first decompressive surgery are eligible for inclusion. The coprimary endpoints are pain measured on a visual analogue scale and physical function measured by the mJOA score at 6 months after surgery. Clinical assessments will be undertaken preoperatively, postoperatively and 3, 6 and 12 months after surgery. We hypothesise that adjuvant therapy with Ibudilast leads to a meaningful and additional improvement in either pain or function, as compared with standard routine care.

**Study design:**

Clinical trial protocol V.2.2 October 2020.

**Ethics and dissemination:**

Ethical approval has been obtained from HRA—Wales. The results will be presented at an international and national scientific conferences and in a peer-reviewed journals.

**Trial registration number:**

ISRCTN Number: ISRCTN16682024.

Strengths and limitations of this studySignificant patient and public involvement in trial design and outcomes planning.A pragmatic approach to patient inclusion criteria was utilised—all patients with modified Japanese Orthopaedic Association score between 8 and 14 and MRI findings of degenerative cervical myelopathy (DCM) who are scheduled for their first surgery for DCM regardless of approach are able to be included.We will explore and compare both clinical and objective findings and validated questionnaire and multiple patient-reported outcomes.A limitation is the need of close patient follow-up and rigorous screening with additional blood tests to comply with drug monitoring and assessments needed.

## Introduction

Here we present the study rationale and design of **Re**generation in **Ce**rvical **De**generative Myelopathy (RECEDE-Myelopathy), the first regenerative medicine trial for degenerative cervical myelopathy (DCM), which aims to test disease-modulating activity of the phosphodiesterase (PDE)3/PDE4 inhibitor Ibudilast as an adjuvant to surgical decompression.

### DCM is a common and progressive condition with devastating impact on quality of life

DCM is the most common cause of spinal cord impairment worldwide,^1 2^ with some estimates of the prevalence as high as 2% of adults.^2–4^ It arises when arthritic or developmental changes in the cervical spine compress the spinal cord, causing a progressive slow-motion spinal cord injury.^5^ As a degenerative pathology the incidence is expected to rise in an ageing population.^6 7^

The consequences of DCM are numerous, varied and often progressive. Symptoms include pain, loss of dexterity, imbalance and frequent falls, incontinence and in extreme circumstances paralysis.^1 8–11^ A recent comparative study found sufferers have among the worst quality of life scores of all chronic disease,^12 13^ and this is likely to also negatively impact on their supporters.^14^ The cost of DCM to society has not been measured yet, but it is likely to be significant. Consequently, improving recovery after surgery is a significant unmet need and there is strong evidence that surgical treatment for DCM is cost-effective.^15^

### Surgery is the only evidence-based treatment for DCM

At present, the only effective treatment for DCM is surgery. While surgery can stop disease progression, the existing damage does not fully recover^16^ and people with DCM retain life-long disabilities with severe impact on quality of life.^12 13^ Many remain unable to return to full time work and reliant on others for day-to-day activities.^17^ Given the severe long-term consequences of DCM, treatment alternatives that promote recovery are desperately needed.

### PDE3 inhibition promotes functional recovery in preclinical DCM

The mitogen-activated protein kinases (MAPKs) play a vital role in intracellular signalling.^18^ In response to extracellular stimuli, such as neurotransmitters, inflammatory factors or stress conditions, this family of interconnected serine/threonine kinases coordinates a diverse range of intracellular processes, including cell differentiation, proliferation and apoptosis, inflammation and stress responses.^19^ This signalling pathway and its modulation have therefore been linked to many diseases including cancer, asthma, stroke, multiple sclerosis (MS) and Alzheimer’s dementia. More recently, preclinical studies, including our own, have demonstrated that its modulation via inhibition of a class of enzymes called PDEs can improve functional recovery and reduce the perception of pain following damage to the central nervous system (CNS).^20–22^

PDEs hydrolyse the intracellular messenger cyclic AMP (cAMP).^20 23^ This results in modulation of MAPK signalling.^24 25^ Inhibition of PDE3 is particularly attractive in DCM as treatment with the selective PDE3 inhibitor cilostozol resulted in improved functional recovery in a rat model of DCM,^26^ likely by improving latent ischaemia.

### Improvements following surgery are associated with axon sprouting, remyelination and immunomodulation

In DCM, tethering and compression of the spinal cord initiates a cascade of secondary injury events, including ischaemia, inflammation and apoptosis that ultimately cause increased neurological deficits.^5 27 28^ The partial reversal of symptoms after surgery highlights an inherent, although attenuated, regenerative capacity of the spinal cord.^16 29^ This is echoed by postmortem studies and our preclinical data, which indicate that neurological recovery following decompression is associated with axonal plasticity, remyelination and modulation of the immune response.^29–31^ Enhancing axonal plasticity and remyelination is therefore key to improving outcomes after DCM.^32^

### PDE4 inhibition can promote functional recovery and modulate pain in preclinical models

PDE4 is another isoform of PDE inhibitors, which has demonstrated preclinical benefits on axon outgrowth^20^ and remyelination.^22^ The best characterised application of PDE4 inhibitors involves preclinical models of traumatic spinal cord injury using a drug called rolipram.^20 21^ Unanimously, these have demonstrated that modulation of the PDE4 cascade is able to benefit recovery. In addition, our own work demonstrated that inhibition of PDE4 is able to stimulate the regenerative response of a CNS stem cell population termed oligodendrocyte progenitor cells and engage in remyelination,^22^ a process that has been observed in postmortem spinal cords affected by DCM.^30^

PDE4 inhibition also has a role in modulating the perception of pain. Central to the development and maintenance of chronic pain syndromes is glial activation within the CNS, which enhances pain sensitivity via neuronal–glial interactions.^33^ Modulation of MAPK via PDE4 inhibition has demonstrated a reduction in pain in several preclinical models.^34–37^ Bao *et al* (2011) found that PDE4 inhibition improved not just motor recovery but also resulted in a reduction in neuropathic pain in a rat model of spinal cord injury.^38^ PDE4 inhibition also has an anti-inflammatory effect, increasing cAMP production in leucocytes and therefore reducing the release of tumour necrosis factor-alpha, a potent inflammatory mediator and peripheral pain stimulus.^39^

### Ibudilast is a potent PDE4 inhibitor with an excellent human safety profile

The majority of preclinical studies described have used rolipram for PDE4 inhibition. While rolipram is a potent and selective PDE4 inhibitor, experience from translational trials, most recently in MS,^40^ has demonstrated poor tolerability in humans due to significant nausea and vomiting. The MS trial had to be terminated due to a lack of efficacy and poor tolerability. Additionally, preclinical evidence has demonstrated a narrow therapeutic window, with potentially adverse neurological sequalae if missed.

An alternative is Ibudilast (MN-166).^23^ Ibudilast is a potent PDE4 inhibitor, with additional PDE3 and PDE5 receptor activity. Modulation of PDE3 is also attractive in DCM as it led to improved function in a preclinical model of DCM.^26^ Another attractive feature of Ibudilast is that it has been in clinical use for over 20 years for the treatment of asthma and poststroke dizziness, without tolerability issues.^41^

Ibudilast is currently under investigation for a number of other neurological conditions, including alcohol (NCT03489850) and methamphetamine (NCT01860807) addiction, glioblastoma (03782415), amyotrophic lateral sclerosis (ALS)^42^ and MS^43^ in a series of double-blind, placebo randomised controlled trials.

For ALS, a single Phase I/II trial has been completed. Two ALS cohorts of early stage disease and advanced stage disease requiring ventilation were randomised 1:1 to receive Ibudilast or placebo. Overall, the primary endpoint of safety and tolerability was met. In the early stage disease takers, Ibudilast was associated with a significant increase in survival, and delayed requirement for ventilation.^44^ Treatment effects were linked to per-protocol adherence to therapy.^45^ A Phase III trial is now planned.

For MS, two phase II trials have been completed. The first one evaluated relapsing remitting MS; while it did not prevent the development of new brain lesions, it slowed the progression of brain atrophy in a dose-dependent fashion. The second one, a follow-up study in progressive MS, found that Ibudilast significantly slowed the progression of brain atrophy.^46^

Of note, typical daily dosing in these trials ranged from 60 to 100 mg, which is greater than the currently licensed dosing of 10–20 mg per day for routine clinical practice. While trials confirmed overall tolerability and safety for use of Ibudilast in these doses in humans, findings do indicate a dose-dependent relationship for gastrointestinal side effects, such as nausea, and headaches and, in a minority of cases, this led to discontinuation of therapy by participants.

### RECEDE-Myelopathy

RECEDE-Myelopathy is a multicentre, double-blind, randomised, placebo-controlled trial assessing the efficacy of Ibudilast as an adjuvant treatment to decompressive surgery for DCM. The specific mechanism of action of Ibudilast is highly suited to address both functional outcome and neuropathic pain in DCM. Therefore, prompted by the direct involvement of people with DCM in designing the study, RECEDE-Myelopathy has an infrequently used study design of two coprimary endpoints. It is designed and powered to detect response of patients to Ibudilast with regards to function or pain, independently, as well as a response to both endpoints. We hypothesise that Ibudilast promotes functional outcome and reduces pain in surgically treated DCM.

## Methods

### Study design and objectives

RECEDE-Myelopathy is a multicentre, double-blind, randomised, placebo-controlled trial assessing the efficacy of Ibudilast as an adjuvant treatment to decompressive surgery for DCM. Participants will be randomised to receive either 60–100 mg Ibudilast (interventional arm) or placebo (control arm) starting within 10 weeks prior to surgery and continuing for 24 weeks after surgery for a maximum of 34 weeks of treatment. Preoperative treatment may leverage the effects of inhibition of PDE3, while postoperative treatment aims at regeneration-inducing effects outlined above. The primary objective will be to compare improvement in pain or physical function at 6 months after surgery between the two arms of the trial. We hypothesise that adjuvant therapy with Ibudilast leads to a meaningful and additional improvement in either pain or function, as compared with standard routine care (decompressive surgery). Planned start date for study recruitment is September 2021, with planned end being September 2025.

### Patient and public involvement (PPI)—aligning research with patient priorities

The involvement of public and patients representatives in research is recognised to be of key importance to ensure it delivers meaningful, practice-changing information.^47–50^ As with many fields, this has been a problem for DCM.^51–53^ To address this issue, we founded Myelopathy.org, the first and so far only charity for people with DCM. While in its infancy, the platform has become an international focus for people with DCM, hosting a peer-to-peer support community (Myelopathy Support) of over 2000 users.^54^ This has enabled larger-scale insights into the perspective of individuals with DCM,^17 55 56^ and ultimately led to RECODE-DCM, a James Lind Alliance-led initiative to identify and define the research priorities for DCM^51^ (https://aospine.aofoundation.org/research/recode-dcm)

### Definition of recovery priorities for people with DCM

AO Spine Research Objectives and Common Data Elements for Degenerative Cervical Myelopathy (AO Spine RECODE-DCM) is an international initiative to create a 'Research Toolkit' to help improve and accelerate knowledge gained in DCM and help to improve outcomes. As part of RECODE-DCM, a focus group of people with DCM was created with the objective to develop recovery domains. These were subsequently prioritised via an international, online survey (n=485).^10^ In contrast to the research focus to date,^52 57^

pain emerged as the number one recovery priority, closely followed by hand, and walking function. Consequently, the development of adjuvant treatments for DCM should be most usefully focused on reducing pain and improving limb function.

### Patient screening and eligibility

A summary of the study flow diagram, including full inclusion and exclusion criteria, is presented in figure 1. In summary, adults (aged 18–80) with a diagnosis of DCM (participants must have at least one MRI indicator, clinical symptom and neurological sign from table 1 to be eligible for inclusion) and a disease severity of modified Japanese Orthopaedic Association (mJOA) score 8–14 inclusive, scheduled for their first decompressive surgery, will be approached to consider participation in RECEDE-Myelopathy.

**Table 1 T1:** Trial criteria for diagnosis of DCM

MRI indicators	Clinical symptoms	Neurological signs
Effacement of cerebrospinal fluid (CSF) and deformation of cord	Numb hands	Pyramidal weakness
T1 signal change	Clumsy hands	Hyper-reflexia
T2 signal change	Bilateral arm paraesthesia	Positive Hoffman sign
Segmentation of T2 signal change	Gait impairment	Upgoing plantar response
Reduction in transverse area of cord	Lhermitte’s phenomenon	Atrophy of intrinsic hand muscles
	Weakness	Spasticity/clonus
		Broad based, unstable gait

Participants must have at least one MRI indicator, clinical symptom and neurological sign to be eligible for inclusion.

DCM, degenerative cervical myelopathy.

**Figure 1 F1:**
[figure not shown]
Trial flow chart. Eligible and consenting participants will be randomised to an intervention or control arm and followed up for 12 months after surgery. DCM, degenerative cervical myelopathy; IMP, investigational medicinal product.

Eligibility will be further assessed against exclusion criteria, largely dictated by safety requirements for use of Ibudilast, and in precluding masking of treatment effects. This includes, concomitant lumbar canal stenosis or other neurological condition, presentation with symptoms due to trauma (eg, central cord syndrome), a history of allergy to Ibudilast, any of its formulation or that of the placebo, pregnancy, unwillingness to use reliable contraception, active malignancy, liver impairment or thrombocytopaenia. The latter will be assessed via serum biochemistry and haematological assessment. A full list of exclusion criteria can be found in table 2.

**Table 2 T2:** Exclusion criteria

1	Previous surgery for degenerative cervical myelopathy
2	Degenerative cervical myelopathy symptoms due to cervical trauma, determined at the discretion of the investigator
3	Hypersensitivity to Ibudilast or any of the formulation components
4	Evidence of acute hepatitis, clinically significant chronic hepatitis or evidence of clinically significant impaired hepatic function through clinical and laboratory evaluation (including alkaline phosphatase (ALP) > 1.5 × upper limit of normal (ULN); alanine transaminas (ALT) or aspartate transaminase (AST) > 2 × ULN; gamma-glutamyl transferase (GGT) > 3 × ULN)
5	Evidence of thrombocytopaenia at screening through laboratory evaluation including platelet count <5000
6	Active malignancy defined as a history of invasive malignancy, except if the patient has received treatment and displayed no clinical signs and symptoms for ≥5 years
7	Recent history (≤3 years) of chemical substance dependency or significant psychosocial disturbance that may impact the outcome or trial participation
8	Female patients with childbearing potential who are unwilling or unable to use reliable methods of contraception
9	Female patients who are pregnant, lactating or planning pregnancy during the course of the trial
10	Inability to comply with trial procedures or follow-up schedule including investigational medicinal product (IMP) regime
11	Unable to take gelatin-based product
12	Participation in another clinical trial of an investigational medicinal product (CTIMP) or device trial ≤30 days before the time of recruitment
13	Functional disability from a concomitant neurological disease that would mask the symptoms of degenerative cervical myelopathy, determined at the discretion of the investigator. Including but not limited to stroke with a residual disability, cerebellar ataxia, Parkinson’s disease, symptomatic lumbar stenosis and multiple sclerosis
14	Resting pulse <50 bpm, sinoatrial or atrioventricular block, uncontrolled hypertension or corrected QT interval (QTcF) >450 ms
15	History of stomach or intestinal surgery or any other condition that could interfere with, or is judged by the investigator to interfere, with absorption, distribution, metabolism or excretion of IMP
16	Unable to converse, read or write English

IMP, investigational medicinal product.

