### Treatment description and dosage modification

The investigational medicinal product (IMP) is a 24–34-week course of Ibudilast or matched placebo in an escalating dosage regimen up to a maximum of 100 mg daily if tolerated. The escalating dosage regimen is to minimise gastrointestinal side effects. Ibudilast is available in 10 mg capsules, and therefore the IMP will be provided as such. The placebo is identical in shape, size and colour to the Ibudilast capsule, and participants will be provided with the same instructions.

Participants will start treatment within 10 weeks prior to surgical decompression and will continue taking drug for up to 24 weeks postsurgery. The excretion half-life of Ibudilast is approximately 20 hours. The IMP will be taken in divided doses, twice daily, morning and evening, for a maximum of 34 weeks. Because this is the first surgical trial with Ibudilast, and to mitigate any potential interference on the coagulation system, treatment will be halted 5 days prior to surgery and resumed at the previous maximum dose right after operation.

Ibudilast is associated with gastrointestinal side effects, such as nausea and dyspepsia. Alongside dose escalation, participants will be instructed to take trial medication with food or within an hour of eating to improve gastrointestinal tolerability. In the event of minor gastrointestinal complaints, participants will be offered symptomatic treatment in the first instance, in conjugation with ongoing IMP therapy. If this is unsuccessful, or not agreeable to participants, the trial therapy will be decreased in decrements of 20 mg every 5 days, until a tolerable dosing level is achieved, or the drug is stopped. If a participant cannot tolerate a minimum daily dosage of 60 mg despite additional supportive measures, treatment within the trial will be stopped.

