### Adaptive sample size design

The minimum clinically important difference (MCID) for the mJOA is estimated to be between 1 and 2 points.^67^ Although not exclusively validated for DCM, the MCID for VAS neck and VAS arm pain has been calculated for degenerative disease of the cervical spine with values ranging from 8 to 26 mm.^64 65^ Both VAS pain and mJOA improve more than the MCID with surgery alone,^57^ and the amount of change is linked to the pre-operative baseline.^67^ Consequently, in consensus with patients we have determined the MCID of the VAS pain score as being 1 cm and for the mJOA 1 point. This has been modelled to ensure statistical power across all baseline scenarios.

On this basis, a total sample size of 362 participants under equal randomisation will provide 85% power to detect a difference of 1 between treatment arms on the mJOA scale (assuming a SD of 2.89), using a two-sided t-test at a 2.5% significance level to adjust for multiple comparisons.^68^ The trial is also powered to detect a similar difference on the VAS neck pain scale (assuming a difference of 1 and a SD of 2.88).

A blinded interim analysis will be conducted to refine the power calculation. The aim will be to reassess the sample size in time to allow any potential extension and increase in sample size to be put into effect. Reduction in sample size will not be permitted. Any sample size increase will be based on checking the assumption regarding the SD, and will not estimate any treatment effect, hence no subsequent adjustment to future analyses is needed.

Under such a framework, the theoretical optimal time to schedule such an interim analysis would be just as the last patient is recruited under the original sample size (n=362) following which a decision could be taken to either halt or extend recruitment. However, for reasons of practicality a window for the interim analysis will be up to a period of 4 months before reaching the total sample size.

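### The only numeric platelet cut-off in the exclusion list has no unit and under either usual unit does not match the word thrombocytopaenia in its own row

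*Protocol article*

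**What the plan says.** In the protocol article, under Patient screening and eligibility, the exclusion criteria are described as "largely dictated by safety requirements for use of Ibudilast, and in precluding masking of treatment effects". The short list there closes with "active malignancy, liver impairment or thrombocytopaenia", followed by: "The latter will be assessed via serum biochemistry and haematological assessment". No platelet number is attached at that point. The reader is sent to Table 2 for all exclusion criteria.

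Table 2, item 5 reads: "Evidence of thrombocytopaenia at screening through laboratory evaluation including platelet count <5000". This is the only platelet limit in the readable text, and no unit or laboratory reference range accompanies it. The other laboratory and physiological limits in the table can be interpreted as printed. Item 4 uses multiples of the upper limit of normal, for example "alanine transaminas (ALT) or aspartate transaminase (AST) > 2 × ULN", and item 14 gives its limits in bpm and ms.

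Two other places bear on the point. Under Treatment description and dosage modification, a separate precaution is taken: "to mitigate any potential interference on the coagulation system, treatment will be halted 5 days prior to surgery". Table 3 makes a full blood count mandatory at screening and again before surgery.

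**The concern.** An eligibility row that rests on a laboratory result should let two sites reach the same decision on the same count. Item 5 offers one number for that purpose, and without a unit the number has no fixed meaning. The two units in common use give values a thousandfold apart, and neither lies near the boundary that the row's own word describes.

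At stake is consistent application of an exclusion that the article ties to the safety of the drug. A site that applies the printed figure per microlitre would clear a patient whose count lies well below its laboratory's lower limit. A site that works from the word thrombocytopaenia would exclude the same patient. Where this table wants investigator judgement it says so (items 2, 13 and 15). Item 5 does not. It points to laboratory evaluation and one figure.

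**Working it through.** **Is there a figure to reproduce?** No. The article does not derive the threshold from anything. The check is a unit conversion and a comparison with a reference range.

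**Inputs**
- Threshold: 5000, no unit (Table 2, item 5).
- Scale: 362 participants (Adaptive sample size design), used only to turn a share into a number of people.
- Assumption, not in the documents: an adult reference range of 150–400 ×10^9/L taken as the central 95%, varied to 140–450 and 130–350.

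**Unit conversion**
- Per microlitre: 5000 × 10^6 per litre = 5 ×10^9/L.
- In ×10^9/L (the same as thousands per microlitre): 5000 ×10^9/L.

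**Distance from the assumed range.** For a range from L to U, compute 5/L and 5000/U. For the share of a reference-like population below 5 ×10^9/L, use a normal model with mean (L+U)/2 and SD (U−L)/(2 × 1.96).

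| Assumed range (×10^9/L) | 5/L | 5000/U | Mean, SD | z at 5 | Share below 5 | Of 362 |
|---|---|---|---|---|---|---|
| 150–400 | 1/30 | 12.5 | 275, 63.8 | −4.23 | 0.000011 | 0.004 |
| 140–450 | 1/28 | 11.1 | 295, 79.1 | −3.67 | 0.00012 | 0.044 |
| 130–350 | 1/26 | 14.3 | 240, 56.1 | −4.19 | 0.000014 | 0.005 |

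With a lognormal model fitted to the same limits, the share below 5 ×10^9/L is essentially zero. Under the second unit, the share below 5000 ×10^9/L is 1.00 in every row, which is all 362.

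**Reading the result.** Per microlitre, every count from 5 ×10^9/L up to the lower reference limit is low by the laboratory's standard yet clears the printed figure. In ×10^9/L, every normal count falls on the excluded side. This holds across the whole assumed range. Surgical candidates with DCM may have low counts more often than a reference population, so the expected numbers are only a scale. The ratios do not depend on that.

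**The case against.** The strongest reply is that the operative term in item 5 is thrombocytopaenia. The number is introduced by the word including, so it is one listed form of evidence and not the whole definition. The running text also names thrombocytopaenia as an exclusion without any number. An investigator can therefore exclude a patient with a low count that clears the printed figure. This stands. A reader might infer that the criterion is void, or that it excludes nobody or everybody. The documents do not support that: those extremes describe the number taken alone, not the row.

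A reader might also infer that the defect exposes patients with low platelets to spinal surgery. That is not supported either. Patients are already scheduled for decompression when they are approached, and surgical care is left to the treating clinician. The article ties the exclusions to drug safety and to masking of effects. Other protections also exist: the pre-operative halt in dosing, repeated blood counts, and data monitoring committee review of surgical complications. None of them repairs the figure.

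Third, this is an article. Sites work from the full protocol, and Figure 1, which is said to carry the full criteria, was not available for this check. A unit or a digit may have been lost in typesetting or in conversion to text. This stands in part: it cannot be said that sites are using this figure. But units elsewhere in the same table are intact, and restoring either usual unit would not make 5000 usable. Nor is this a detail left to a fuller document. The figure is stated, in a table offered as complete.

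**Conclusion.** The point holds in a limited form. As printed, the one objective cut-off in item 5 is unusable: about 1/26 to 1/30 of the assumed lower limit under one unit, 11 to 14 times the assumed upper limit under the other. It does not match the word thrombocytopaenia beside it. What remains of the criterion is exclusion by judgement, which sites may exercise differently.

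The conclusion rests on the assumed reference range, on these two units being the candidates, and on the table text being complete as read. It does not extend to the CRF, the operational protocol or decisions already made at sites, since none of these is shown. It has no bearing on the sample size, power or significance levels.

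**What to change.** The sponsor's medical lead should reconcile three things for item 5: the figure, its unit and the word thrombocytopaenia. The sources are the full protocol, Figure 1 and the drug safety documents. Table 2 should then be corrected with the unit stated. If the error is confined to the article, a correction to the article is enough.

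If the operational protocol, eligibility CRF or its edit check carries the same figure, correct those as well. Then recheck the screening full blood counts of participants already enrolled against the reconciled criterion. No threshold is proposed here; that is for the sponsor to settle from its own documents.

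The cost is one line in the table and, if needed, one CRF edit check and a listing of counts that the schedule already requires. No new data collection or change to the analysis is involved.
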